## Abstract

**Background:**

Transcranial direct current stimulation (tDCS) has the potential to modulate cortical excitability and enhance the effects of walking training in people with Parkinson’s disease. This study will examine the efficacy of the addition of tDCS to a task-specific walking training to improve walking and mobility and to reduce falls in people with Parkinson’s disease.

**Methods:**

This is a two-arm, prospectively registered, randomized trial with concealed allocation, blinded assessors, participants and therapists, and intention-to-treat analysis. Twenty-four individuals with Parkinson’s disease, categorized as slow or intermediate walkers (walking speeds ≤ 1.0 m/s), will be recruited. The experimental group will undertake a 30-min walking training associated with tDCS, for 4 weeks. The control group will undertake the same walking training, but with sham-tDCS. The primary outcome will be comfortable walking speed. Secondary outcomes will include walking step length, walking cadence, walking confidence, mobility, freezing of gait, fear of falling, and falls. Outcomes will be collected by a researcher blinded to group allocation at baseline (week 0), after intervention (week 4), and 1 month beyond intervention (week 8).

**Discussion:**

tDCS associated with walking training may help improve walking of slow and intermediate walkers with Parkinson’s disease. If walking is enhanced, the benefits may be accompanied by better mobility and reduced fear of falling, and individuals may experience greater free-living physical activity at home and in the community.

**Trial registration:**

Brazilian Registry of Clinical Trials (ReBEC) RBR-6bvnx6. Registered on September 23, 2019

## Background

Parkinson’s disease is the most common movement disorder and represents the second most common degenerative disease of the central nervous system, resulting from the death of dopamine-producing cells in the *substantia nigra* [1]. Disabilities associated with Parkinson’s disease such as bradykinesia, impaired balance, and walking limitations can be present at initial diagnosis and progress over time [1, 2]. In individuals with Parkinson’s disease, while walking speed, step length, and mobility are typically reduced, fear of falling and the number of falls are increased [3, 4]. If walking performance is poor, community activity may be limited, and people may become housebound and isolated from the society. In addition, falls are a major determinant of poor quality of life, reduced mobility, and reduced life expectancy in people affected by Parkinson’s disease [4].

Exercise and walking training have proved to be effective for improving walking and reducing falls early in people with Parkinson’s disease [5–7]. Non-invasive brain stimulation by transcranial direct current stimulation (tDCS), which modulates cortical excitability by applying a direct current to the skull [8], could be associated with walking training and has the potential to enhance its benefits [9]. tDCS can increase the activity of the ventroposterolateral thalamic nucleus and may influence basal ganglia function. In addition, anodal tDCS over the motor cortex alter resting membrane potentials of underlying neurons leading to an increase in cortical excitability, with immediate and long-term effects that have been proposed to help improving motor skills [8, 10, 11].

A Cochrane review [8] examined the effects of tDCS in individuals with Parkinson’s disease. Meta-analyses, based on two trials, suggested that tDCS improves motor skills, measured by the Unified Parkinson’s Disease Rating Scale (UPDRS)—part III—(MD − 14%; 95% CI − 25 to − 4), but has no effect on walking speed (SMD 0.5; 95% CI − 0.2 to 1.2) compared with sham intervention. More recently, a systematic review [12] reported that tDCS provides no clinically important benefits over walking training on walking speed, step length, or cadence in people with Parkinson’s disease. Given that most trials included individuals with mild impairments or did not investigate effects on mobility and falls, the purpose of this randomized trial is to examine the effects of the addition of tDCS to walking training on walking, mobility, and falls in individuals with moderate walking limitations due to Parkinson’s disease. The specific research questions are as follows:
In people with Parkinson’s disease, is walking training associated with tDCS superior to walking training alone for improving walking (speed, step length, cadence, confidence), mobility, and falls?Are any benefits maintained beyond the intervention period?

## Methods

### Design

A prospective, randomized controlled trial with concealed allocation, blinded assessors, participants and therapists, and intention-to-treat analysis will be carried out (Fig. 1). Community-dwelling people with Parkinson’s disease will be recruited from the general community, by means of advertisements and by screening public rehabilitation services and lists of previous observational or cross-sectional research projects. Participants will be randomly allocated into either experimental group (i.e., walking training with tDCS) or control group (i.e., walking training with sham-tDCS). Outcome measures will be collected by trained researchers at baseline (week 0), at the end of the intervention (week 4), and 1 month beyond the intervention (week 8). Measurements and interventions will be conducted during the on phase of medication. Analyses of the inclusion criteria, getting the informed consent, data collection, and statistical analyses will be carried out by researchers, who will be blind to the group allocation. All the participants will be evaluated and receive all the information regarding the interventions in a research laboratory. The study obtained ethical approval from the Institutional Research Ethical Committee (CAAE 06952819.6.0000.5060) of the Universidade Federal do Espírito Santo, Vitória, Brazil. The trial was prospectively registered at the Ensaiosclinicos.gov.br, Registry: RBR-6bvnx6 (www.ensaiosclinicos.gov.br/rg/RBR-6bvnx6/).

**Fig. 1 Fig1:**
[figure not shown]
Design of the trial

### Participants and therapists—inclusion and exclusion criteria

Participants will be individuals with Parkinson’s disease, who will be eligible if they:
Are > 40 years of ageAre able to walk at least 14 m, independently, with or without assistive devicesWalk at speeds ≤ 1.0 m/sHave experienced a freezing episode over the past month, according to the part I of the New Freezing of Gait Questionnaire [13]Have adapted to their current anti-Parkinsonian medication for at least 2 weeksProvide written consent

They will be excluded if they:
Have cognitive deficits, which will be screened by the Mini-Mental State Examination. The cutoff scores are 26 for people with high levels of education, 18 for people with elementary and middle levels, and 13 for illiterate people [14].Suffer from unstable cardiovascular disease or other uncontrolled chronic conditions that would interfere with the safety and conduct of the training and testing protocol or interpretation of the results.Had undergone deep brain stimulation.

Therapists, who will deliver the intervention, will be eligible if they have received training from the research leaders ([name] and [name]), who have more than 10 years of clinical experience in the area of neurological rehabilitation. A research assistant will be responsible for setting the stimulator on active or sham-tDCS, so therapists delivering the intervention will be blind to the group allocation.

### Randomization

Randomization will be computer-generated, by a researcher not involved in participant recruitment, and stratified according to the baseline walking speeds: slow (≤ 0.5 m/s) and intermediate (0.51 to 1.0 m/s) walkers, to ensure an even spread between the groups (1:1 allocation). The allocation of the participants will be concealed in sequentially numbered and sealed in opaque envelopes, prepared prior to the study by a research assistant, who will not be involved in the study. After the baseline measures have been collected, participants will be randomly assigned to the experimental or control group by the treating therapist, after revealing the content of the sealed opaque envelopes. All outcomes will be measured by blinded assessors. All enrolled participants will receive a code, in order to protect confidentiality before, during, and after the trial.

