## Discussion

This trial will examine the efficacy of the addition of tDCS to walking training for improving walking, mobility, and falls in people with Parkinson’s disease. Although previous studies [9, 10, 15, 16, 27] have investigated the combined effect of tDCS and walking training, methodological shortcomings (e.g., design and very small sample sizes), characteristics of interventions (e.g., duration of intervention, type of exercises), and characteristics of the participants (e.g., level of disabilities) prevent drawing clear conclusions, which could help clinicians in their decision-making process. In addition, many trials did not investigate whether benefits carry over to improving mobility and falls. In response to this challenge, a triple-blinded randomized trial will be conducted. High internal validity is expected, due to randomization, concealed allocation, blinding of assessors, participants and therapists, intention-to-treat analysis [28], and appropriate sample size.

Previous studies suggest that tDCS modulates cortical excitability during stimulation by non-synaptic changes of the cells, and increasing evidence indicates that the aftereffects of tDCS are driven by synaptic modification [29]. Synaptic plasticity could, therefore, induce long-lasting excitability changes in the central nervous system. Although the neurophysiological effects of tDCS have been identified and its safety has been proved [29, 30], the clinical effects remain unclear. This trial focuses on identifying the effects of the addition of tDCS on walking parameters commonly affected in individuals with Parkinson’s disease [3, 31]. If neurophysiological benefits of tDCS are carried over to clinical benefits, clinicians will assure an important tool to help reduce disabilities related to the continuous death of dopamine-producing cells in the *substantia nigra*. Less expensive portable devices are currently available, making direct current potentially ideal as an adjunct to other physical interventions [30].

This trial has some limitations. The experimental and control interventions consist of walking exercises delivered three times per week over 4 weeks and, therefore, depend on participants’ motivation, adherence, and commitment. Strategies to encourage participants to comply with the protocol, such as contracts and phone calls, are planned.

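### The treating therapist opens the allocation envelope and assigns the group, so the claimed therapist blinding cannot hold as written

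*Protocol article*

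**What the plan says.** The Randomization section describes how a participant gets from baseline to an arm. A research assistant with no other part in the study prepares the envelopes, and "The allocation of the participants will be concealed in sequentially numbered and sealed in opaque envelopes". Once baseline measures are complete, "participants will be randomly assigned to the experimental or control group by the treating therapist, after revealing the content of the sealed opaque envelopes".

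The section on eligibility of participants and therapists describes a different arrangement: "A research assistant will be responsible for setting the stimulator on active or sham-tDCS, so therapists delivering the intervention will be blind to the group".

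Therapist blinding is then stated as a design feature in three more places:

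- Abstract, Methods: "randomized trial with concealed allocation, blinded assessors, participants and therapists, and intention-to-treat analysis".
- Design: "concealed allocation, blinded assessors, participants and therapists, and intention-to-treat analysis will be carried out".
- Discussion: "a triple-blinded randomized trial will be conducted", followed by "High internal validity is expected, due to randomization, concealed allocation, blinding of assessors, participants and therapists".

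**The concern.** One section has the treating therapist learn the allocation; another has the same therapists blind to it. The design depends on which is followed. Both arms receive walking training with identical electrode placement, and only the current is meant to differ. The contrast isolates the current only if the training is delivered alike in both arms.

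The therapist has real latitude over that training. The Intervention section says it is adjusted to each participant, and Table 1 lets the therapist progress speed, height, distance, hand support, cadence and dual-task load. The section on data monitoring also makes the treating therapists responsible for monitoring doses and compliance. A therapist who knows the arm may, without intending to, push or encourage one group more, or give the arm away to the participant. Comfortable walking speed is open to this, and so are the self-reported secondary outcomes (walking confidence, freezing, fear of falling).

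**Working it through.** No arithmetic decides this point, and nothing in the sample size section bears on it. The check is whether any reading lets both sections stand.

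1. **What the therapist knows under Randomization.** The envelope holds the allocation. The therapist assigns the participant to a named group, experimental or control, after the content is revealed. Even if someone else physically opened the envelope, the person making the assignment would know the group.

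2. **Whether the research assistant restores the blind.** The assistant's role is to set the device. That keeps the arm from a therapist who has not yet learned it. It does nothing for one who already has.

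3. **Where the stimulator-setting assistant learns the arm.** The assistant who prepares the envelopes is described as uninvolved in the study, so that is a different person. After baseline, the only person described as handling an envelope is the treating therapist. As written, the assistant has no stated source for the arm other than the therapist who is supposed to be blind.

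4. **Readings that would reconcile the two sections.**
   - *The envelope holds only a device code.* No section says so. The only code mentioned is a participant identifier for confidentiality, and the sentence names the two groups.
   - *The therapist who opens the envelope is not the one who treats.* The text says treating therapist, and no second therapist role is described.

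5. **Which claims depend on this.** Therapist blinding in the abstract, Design, eligibility section and Discussion, and the triple-blinded label in the Discussion.

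6. **Exposure if the Randomization text is followed.** Sessions per participant: 3 per week × 4 weeks = 12. Participants: 24. Participant-sessions: 24 × 12 = 288. This is an upper limit. It assumes every allocation was made this way and that the allocating therapist also delivers the sessions.

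7. **What is not affected.** Concealment before assignment is not challenged here: envelopes are sealed, opaque and numbered, and are opened after baseline. Blinding of assessors and of the analyst is stated separately.

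**The case against.** The strongest reply is that this is one badly worded sentence in a condensed article. Every statement of intent points to blinded therapists, and the eligibility section gives a concrete mechanism. The envelope may in practice have carried a code. Other safeguards also remain: assessors and analyst are blinded, participants are not told their arm, the primary outcome is a timed 10-m walk, and both arms are to receive the same training.

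Part of this stands. The article does not prove that therapists were unblinded, so the exposure must be stated as conditional, and the bias has no known size or direction. The remaining route is indirect, through how training is progressed and how participants are cued.

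The rest does not rescue the text. This is not a detail left to a fuller document. The article states two incompatible procedures, and a fuller document would have to contradict one of them. Blinded assessment and blinded analysis protect measurement and reporting; they cannot undo a difference produced during treatment. Participant blinding itself relies partly on the therapist not knowing or not disclosing the arm.

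**Conclusion.** The concern holds. As written, the Randomization section defeats the therapist blinding claimed elsewhere, and nothing in the article reconciles the two. If that section is followed, up to 24 of 24 participants and all 12 sessions each are exposed to a therapist who may know the arm, and the active–sham contrast on walking speed may mix the effect of current with therapist behaviour and participant expectation. The size of that effect cannot be derived from the document. The conclusion rests on two readings of the text: that the envelope shows the group, and that the treating therapist is the person who delivers training. It must be corrected, because the Discussion counts therapist blinding among the reasons to expect high internal validity.

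**What to change.** Rewrite the assignment sentence under Randomization along these lines: after baseline, the research assistant who sets the stimulator opens the next envelope in the participant's speed stratum, sets the device to active or sham out of sight of therapist and participant, and keeps the allocation; treating therapists and assessors do not handle the envelopes. State that this assistant is not the one who prepared the envelopes. An envelope holding only a device code, with the key kept from therapists, would serve equally well.

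The Trial status section says recruitment began in September 2019, so the sponsor should also establish and report which procedure was used for anyone already randomised. If therapists saw the group, record this and withdraw the therapist-blinding and triple-blinded statements for the trial, making clear which participants were affected.

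The cost is one sentence and a change of who opens the envelope. The assistant is already in the plan, so no new staff should be needed, provided that person is available at allocation, which the article does not state. Sample size and analysis are unchanged.

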### Intervention

The experimental group will undertake a task-specific walking training associated with tDCS, 30 min per day, 3 days per week, over 4 weeks, i.e., 12 sessions of tDCS. A stimulator (DC-Stimulator Plus, NeuroConn, Ilmenau, Germany, or Neuroeletrics STARTIM tCS, Barcelona, Spain) will deliver a continuous direct current by a saline-soaked pair of surface sponge electrodes (size of electrodes 35 cm^2^). The anode will be placed at the Cz position on the scalp, corresponding to the location of the supplementary motor area, in accordance with the International EEG 10/20 system [15, 16]. The cathode will be positioned over the left supraorbital area. Participants will receive electrical stimulation of 2 mA, during the walking training. The 30-min sessions of task-specific walking training will include the practicing part of the task (about 10 min), where the muscles are working in a manner similar to a full task performance and practicing the whole task (about 20 min) [17]. Table 1 shows the ten walking activities of the task-specific walking training, which will be individually tailored for each participant.

**Table 1 Tab1:** Activities of the task-specific walking training

Activity	Type	Practice	Progression
Step on block	Segmented	Swing	Diminishing hand support and increasing speed, height, and/or distance
Stand on one leg then perform plantarflexion		Stance	Diminishing hand support and increasing speed
Step sideways		Lateral movement	Diminishing hand support and increasing speed and/or distance
Step sideways on a block		Lateral movement	Diminishing hand support and increasing speed, height, and/or distance
Walk on footprints	Complete	Whole task	Increasing step length
Walk with an auditory cue		Whole task	Increasing cadence
Walk and turn		Whole task	Increasing speed
Walk and cross obstacles		Whole task	Increasing speed
Dual-task walk		Whole task	Increasing speed and cognitive/motor demands
Overground and treadmill speed walk		Whole task	Increasing speed

The control group will undertake the task-specific walking training associated with a sham-tDCS. The control group will receive the same walking training, electrode positioning, and testing schedule as the experimental group. This will avoid bias related to the type and amount of attention given to the participants. If the addition of tDCS proves to be effective, the control group may receive the experimental training program after the experiment is complete.

The intervention will be undertaken in Clinics of Physiotherapy at the Universidade Federal do Espírito Santo. To encourage the participants to comply with the protocol, both groups will be asked to sign a symbolic contract of commitment to the proposed protocol. Participants will not be informed whether they are receiving tDCS or sham-tDCS.

### Primary outcome

The primary outcome is comfortable walking speed, measured by the 10-m Walk Test, and reported in m/s. The participants will be instructed to walk at their “comfortable speed” along a 14-m hallway, and the time to cover the central 10 m will be recorded with a digital stopwatch and converted to speed [18]. After a practice trial, the value obtained during a single test will be used for analysis [19].

### Secondary outcomes

Secondary outcomes are walking step length, walking cadence, walking confidence, mobility, freezing of gait, fear of falling, and falls.

Walking step length and cadence will be measured using the 10-m Walk Test. Step length will be calculated by dividing the covered distance, i.e., 10 m, by the number of steps to cover the distance, and reported in meters. Walking cadence will be calculated by dividing the number of steps by the time to cover the distance, i.e., 10 m, and reported in steps/min.

Walking confidence will be measured using the Brazilian version of the modified Gait Efficacy Scale and reported as scores ranging from 10 to 100. This scale is a 10-item measure that addresses the perception of the level of confidence in walking during challenging circumstances. The items include walking on a level surface and on grass, stepping over an obstacle, stepping up and down a curb, ascending and descending stairs (with and without a handrail), and walking over a long distance. The items are individually scored on a 10-point Likert scale, with 1 indicating “no confidence” and 10 indicating “complete confidence,” [20, 21].

Mobility will be measured by the Timed-up and Go Test (TUG) and reported as seconds. The participants will be seated in a chair with their backs against the chair back. On the command “go,” the participants will be instructed to rise from the chair, walk 3 m at a comfortable and safe pace, turn, walk back to the chair, and sit down. After a practice trial, the value obtained during a single test will be used for analysis [19, 22].

Freezing of gait will be measured using parts II and III of the New Freezing of Gait Questionnaire and reported as scores ranging from 0 to 28, where higher scores indicate worse episodes of freezing. The New Freezing of Gait Questionnaire is a reliable tool to detect and evaluate the impact and severity of freezing of gait, when applied to patients (ICC = 0.88) or caregivers (ICC = 0.97) [13].

Fear of falling will be measured using the Brazilian version of the Falls Efficacy Scale – International (FES-I Brazil) and reported as scores ranging from 16 to 64, where higher scores indicate greater fear of falling. The FES-I Brazil measures the fear of falling during 16 activities of daily living and has appropriate internal consistency (*α* = 0.93) and intra- and inter-examiner reliability (ICC = 0.84 and ICC = 0.91) [23].

The number of falls will be recorded by the use of a “falls diary” [24], and the proportion of fallers in each group will also be compared. All participants will receive weekly calendars on entry to the study, with instructions to record the following events: number of falls, visits by or to nursing and allied health personnel, and hospitalizations. Participants will be asked to return the completed calendar weekly to a researcher unaware of the group allocation.

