### Sample size estimation

Twenty-four participants will be recruited, with walking speed as the primary outcome. The sample size has been calculated, to reliably detect a between-group difference of 0.18 m/s in walking speed, with 80% power, at a two-tailed significance level of 0.05. In previous trials [9, 16, 25] with similar samples of community-dwelling people with Parkinson’s disease who received tDCS associated with walking training, the mean walking speed of the participants was 0.73 m/s (SD 0.15 m/s), measured by a timed-walking measure. The least number of participants needed to detect a 0.18 m/s difference between two independent groups, which would indicate a change in the UPDRS walking category [26], is 11 per group, i.e., 22 participants in total. Based on the assumption that about 10% of participants may drop out during the study, a target of 24 participants in total has been set.

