### Statistical analyses

Data collection will yield eight variables: walking speed (m/s), walking step length (m), walking cadence (steps/min), walking confidence (modified Gait Efficacy Scale score; 10–100), mobility (TUG; seconds), freezing of gait (New Freezing of Gait Questionnaire; 0–28), fear of falling (FES-I Brazil score; 16–64), and number of falls. There are two factors (group × time), with repeated measures on the time factor. Two-way analyses of variance with repeated measures at all time points for all outcomes will be reported to evaluate the statistical significance of the between-group differences. The mean between-group differences, along with 95% confidence intervals, will be reported for all outcomes. The effect of the intervention will be calculated based on intention-to-treat analyses.

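### Falls are compared as a raw count and as a proportion of fallers, with no allowance for weeks observed, although about 10% dropout is expected and the weekly calendars already supply the person-time

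*Protocol article*

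**What the plan says.** All of this is in the protocol article.

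- **Secondary outcomes** fixes two fall measures. The first is a count: "The number of falls will be recorded by the use of a “falls diary". The second is binary: "the proportion of fallers in each group will also be compared". No rate, and no time window for the proportion, is given.
- The same section describes the data source: "All participants will receive weekly calendars on entry to the study", and "Participants will be asked to return the completed calendar weekly to a researcher unaware of the group allocation". The number of weeks observed is therefore known for each person.
- **Statistical analyses** lists the number of falls among eight variables. It assigns all of them a group-by-time repeated-measures ANOVA and a difference in means with a 95% interval. It also states: "The effect of the intervention will be calculated based on intention-to-treat analyses".
- **Sample size estimation** assumes that "about 10% of participants may drop out during the study".
- **Design** sets the later assessments "at the end of the intervention (week 4), and 1 month beyond the intervention (week 8"), and **Intervention** sets the training at "30 min per day, 3 days per week, over 4 weeks, i.e., 12 sessions of tDCS".

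**The concern.** A count of falls, or a yes/no for any fall, means the same thing in two people only if they were watched for the same time. The plan expects some people to leave and commits to analysing by intention to treat, yet neither fall measure takes observed time into account.

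There are two ways to handle an early leaver under the stated methods, and both have a cost:

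- **Kept in with a partial count.** A few weeks of falls stand in for a full period, and someone with no fall before leaving is counted as a non-faller. The arm with more or earlier leavers then looks better on falls without any treatment effect.
- **Left out because the repeated measures are incomplete.** The undercount disappears, but the comparison is restricted to completers and is no longer intention to treat.

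A weekly calendar not returned by someone still in the trial raises the same difficulty. Falls are a secondary outcome, but reducing them is part of the aim in the Abstract and of the first research question in the Background. The Discussion also notes that many trials did not look at falls.

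**Working it through.** **1. The plan's own figures.** The article gives no figure for falls. Its sample size for walking speed reproduces with the normal formula: 2 × (1.960 + 0.842)² × (0.15/0.18)² = 10.90, so 11 per group and 22 in total. Dividing by 0.9 gives 24.4, against the stated 24. Expected dropout is 24 × 0.10 = 2.4, so 2 to 3 people.

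**2. Assumptions for the illustration.** 12 per arm (24 at 1:1), an 8-week window, the same constant fall rate in both arms, all dropouts in one arm, and their partial counts kept in the analysis. The article states neither the split of dropouts between arms nor any fall rate.

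**3. Raw count.** With d dropouts leaving at week w, the expected ratio of that arm's count to a fully observed arm's count is [(12 − d) × 8 + d × w] / 96.

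| Two dropouts leave at week | Observed person-weeks | Count ratio |
|---|---|---|
| 0 | 80 of 96 | 0.83 |
| 2 | 84 of 96 | 0.88 |
| 4 | 88 of 96 | 0.92 |
| 6 | 92 of 96 | 0.96 |

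Over the same weeks, one dropout gives 88/96 = 0.92 to 94/96 = 0.98, and three give 72/96 = 0.75 to 90/96 = 0.94.

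**4. Proportion of fallers.** At a rate r per week, the chance of at least one fall in w weeks is 1 − exp(−r × w). Take r = 0.125 and two dropouts at week 2. A fully observed person has 1 − exp(−1) = 0.632, and a dropout has 1 − exp(−0.25) = 0.221. The arm's expected proportion is (10 × 0.632 + 2 × 0.221)/12 = 0.564, which is 6.8 points too low. For two dropouts leaving between weeks 1 and 4, the shortfall is:

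| Assumed falls per person-week | Shortfall (percentage points) |
|---|---|
| 0.05 | 2.5 to 4.7 |
| 0.125 | 4.0 to 8.6 |
| 0.25 | 3.9 to 10.7 |

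**5. Rate per observed week.** For two dropouts at week 2, expected falls are 84r over 84 observed weeks, so the arm's rate is r, the same as 96r/96 in the other arm. The ratio is 1.00, and the same cancellation holds for every row of the count table.

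**6. How often the imbalance arises by chance.** If two dropouts are equally likely to be any of the 24, the chance that both are in the same arm is 11/23 = 48%, or 24% for a given arm. With three, equal numbers are impossible.

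**7. Size against sampling error.** The standard error of a difference in proportions at 0.632 with 12 per arm is √(2 × 0.632 × 0.368/12) = 0.197. The 6.8-point shortfall is 0.068/0.197, about 0.35 of a standard error.

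**The case against.** The strongest reply is that a protocol article may leave the handling of incomplete diaries to an analysis plan, and that the bias is conditional. It needs dropout that differs between arms in number or timing, which an overall 10% does not imply. Participants and therapists are blinded and the walking training is the same in both arms, so the document gives no reason to expect one arm to lose more people. Chance imbalance has no preferred direction, and the distortion is small beside the sampling error in 24 people. An ANOVA on complete cases would exclude early leavers, not score them as low fallers.

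Most of this stands, and it limits the size of the point. It does not remove it. The two fall measures and the ANOVA are stated choices, not gaps, and neither measure uses observed time. Excluding incomplete participants exchanges the undercount for a departure from intention to treat.

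A reader might infer more from the Design section: that follow-up is timed from the end of the intervention, so that someone who stops training early also has a shorter follow-up. The documents do not support this. The same sentence fixes the assessments at weeks 4 and 8, and the intervention is fixed at 4 weeks. Nothing moves a visit for someone who stops early. Nor does the article say that calendars stop when training stops; they go to all participants at entry and their weekly return is not tied to sessions.

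**Conclusion.** The point holds as a weakness in the choice of fall measures. As stated, they make no allowance for observed weeks in a trial that expects to lose 2 to 3 of 24 people, while the weekly calendars supply exactly the information needed.

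With both of two dropouts in one arm and partial counts retained, equal true fall rates would appear as a count ratio of 0.83 to 0.96 for leaving at weeks 0 to 6. The proportion of fallers would be too low by a few points, up to about 11, at the assumed rates for leaving at weeks 1 to 4. These figures illustrate a one-sided scenario and do not predict what this trial will show. With dropout equal in number and timing, the expected bias is zero. The primary outcome is not affected. The case for changing the plan is that a better comparison is available at almost no cost, not that the falls result is already known to be biased.

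**What to change.** In Secondary outcomes and Statistical analyses:

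1. Compare falls as a rate per person-week of returned calendars over weeks 0 to 8, for example by negative binomial regression with the log of observed weeks as offset. Include every randomised participant with any returned calendar. This would replace the ANOVA for this outcome.
2. Compare fallers over the same window by a method that allows for observed time, for example time to first fall, censored at the last returned calendar.

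No new data are needed. The cost is a few sentences of protocol text and slightly more analysis. Both methods assume that early loss is unrelated to fall risk, and that assumption should be stated with the result. The visit schedule needs no change, since weeks 4 and 8 are already fixed.
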